#### Parent-reported parenting outcomes

Parent-rated parenting stress associated with core and comorbid symptoms is measured using the Autism Parenting Stress Index^30^ and parenting self-efficacy is measured using the Child Adjustment and Parent Efficacy Scale-Developmental Disability Parent Efficacy subscale,^31^ a 16-item scale assessing confidence in managing specific child behaviours. The Short Warwick-Edinburgh Mental Wellbeing Scale^32^ assesses parent reports of their own well-being. The short version of the Parenting Scale^33^ is used to measure self-reported lax and overreactive parenting practices.

#### Sample characterisation measures

Demographic information about the family is obtained at baseline. Autism severity is measured at baseline only using the parent-reported Social Communication Questionnaire-Lifetime version,^34^ along with the *Autism Diagnostic Observation Schedule,* second edition (ADOS–2).^35^ The ADOS–2 is the gold standard observation for assessing autism symptoms and is administered by trained researchers. The *Adaptive Behaviour Assessment System*, third edition^36^ is completed by parents at baseline and measures three broad domains of adaptive skills and functioning (conceptual, social and practical), resulting in a General Adaptive Composite score.

#### Intervention-related measures

Attendance at intervention sessions and retention in the intervention are recorded. Satisfaction with the content and delivery of both interventions is measured using questionnaires developed for study.

#### Health economic measures

Parental well-being and daily emotions are measured using the Office of National Statistics (ONS) Personal Wellbeing questions,^37^ which ask about life satisfaction, worth, happiness and anxiety. The 5-level EQ-5D^38^ is used to measure parent reports of their own health-related quality of life, and index-based values are available to enable quality-adjusted life years (QALYs) calculations to be used in the cost-effectiveness analysis.

An adapted version of the Client Service Receipt Inventory (CSRI)^39^ measures service use and cost-related impacts at baseline and post intervention, to inform the cost-effectiveness analysis. Parents are asked to retrospectively identify all public, private and voluntary sector services used by the child, as well as services used by other family members that are linked to the child’s autism or emotional and behavioural difficulties. The CSRI also includes information on unpaid support and employment impacts on other family members. The facilitators delivering the interventions track their time spent on intervention-related activities and travel costs to be used in costing the interventions.

### Procedure

Children between the ages of 4 and 8 years with a diagnosis of ASD are recruited to the study from participating services following referral via local autism diagnostic teams, education professionals, support groups and consented databases. Potential participants can also self-refer. As the intervention content is adapted based on child verbal ability, the groups are run separately with parents of minimally verbal and verbal children within each of our localities. Therefore, the blocks of 10–18 families recruited for allocation to condition will be stratified by verbal ability level (minimally verbal: defined by ADOS–2 Module 1 vs verbal children: defined as ADOS–2 Module 2 or above) and by locality (Croydon, Bromley) as part of the recruitment procedure.

After initial contact and prescreening for eligibility, research staff obtain informed consent and conduct baseline assessments to confirm eligibility. All families are assigned a unique participant ID. Questionnaire measures are completed online or in hard copy depending on the parent’s preference. Other measures are completed during a visit to the research setting, over the phone or at the child’s school. Baseline assessments with families are conducted up to 2 months prior to randomisation. With parental consent, teachers are asked to complete questionnaires about the child’s emotional and behavioural difficulties at school. Post intervention assessments are conducted after the completion of the intervention. Outcome measures are sought for all families regardless of their participation in the treatment provided.

There are separate research and clinical teams who are based in different buildings and have separate supervision structures. The assessments and interventions are conducted in a way to avoid inadvertent divulging of information that could reveal allocation status. The location and materials used during the research assessments are different in type and location to those used for the intervention sessions, avoiding any familiarity effect for parents. Researchers involved in conducting the assessments and rating outcome measures are blinded to intervention content and participant condition. Group facilitators are blinded to primary outcome measurement.

### Data management, confidentiality and access

All data in the trial are anonymised. All paper records are filed anonymously by the participant’s unique study number in secure locked cabinets in the Department of Child and Adolescent Psychiatry, IoPPN, King’s College London. Consent forms are stored separately. Personal details (eg, name, address and telephone numbers) are stored in a separate encrypted database and linked by initial, date of birth and unique participant ID number. Some records from the feasibility phase are stored securely at York University.

Data from paper case report forms are entered on SPSS databases and along with other electronic data, stored on a King’s server folder that is accessible only to the research team. Double data entry will be completed on at least 10% of all entered data, and quality checks will be conducted. The principal investigator, trial statisticians and other members of the study team have access to final datasets and will undertake analysis as appropriate and necessary. Any arrangements for other researchers to have access to the data will be negotiated separately and the Central Office of Research Ethics Committee will be informed.

### Statistical analyses

A statistical analysis plan has been written by the trial statisticians (AP and DS) and will be approved by the chief investigator and the Data Monitoring Committee (DMC) prior to any analysis being undertaken. The analyses will be carried out using Stata.

In accordance with Consolidated Standards of Reporting Trials guidelines, we will report the flow of participants through the trial. Descriptive statistics of recruitment, drop-out and completeness of assessments and interventions will be provided. Satisfaction and fidelity of the intervention will also be reported descriptively. Baseline characteristics will be presented by group.

The main analysis will be via intention-to-treat, including all participants who were randomised. It will use statistical techniques for handling missing outcome data under a missing at random assumption, and multiple imputation for missing measures will be considered. We will test for a between-group change in the primary outcome at post intervention, using analysis of covariance (ANCOVA) regression predicting outcome where post intervention is also covaried for baseline. Dummy variables will be used to account for randomisation stratification and the clustering effects of groups. The distribution of the primary outcome at baseline will be examined for evidence of floor effects. Where floor effects are present, a generalised mixed model/structural equation modelling setup, in which both baseline and post intervention are modelled as potentially censored response variables, will be used with a covariance between equations that yield the ANCOVA estimate of treatment effect in the absence of censoring. Secondary outcome measures will be analysed in the same way. Analysis of all post intervention treatment effects will be undertaken after all post intervention outcome measures are completed. Trial statisticians will remain blinded until after the primary and secondary outcomes are analysed.

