Parents who were interviewed reported that the research procedures were acceptable, although some felt the assessment process was lengthy. Prior to commencing the pilot RCT, two proposed outcome measures were removed to reduce burden on families (see our ISRCTN record for a log of outcome measures tested during the feasibility phase). For some parents, there appeared to have been a lack of clarity about the difference between the research and clinical teams and who they would have contact with at each stage of the study. This led to amendments in the information given to parents to help make this distinction clearer. Findings from the qualitative interviews also indicated that most parents reported that they found the groups helpful and that they enjoyed meeting other parents in a similar situation. Feedback on the structure, timing, course materials and homework led to modifications to the Predictive Parenting intervention. For example, changes were made to make the groups more accessible and relevant to parents of children with lower levels of verbal ability. The study design was also amended by increasing the number of families in each group (from six to eight) as it was a more efficient way to recruit and deliver the interventions. The increased group size was not thought to disrupt the intervention; indeed, the slightly larger sizes may be helpful for group dynamics. Further details on the feasibility study can be provided on contact with the research team.

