### Trial design

The study is a parallel-group pilot RCT. Participating families are allocated to one of two treatment arms (Predictive Parenting or psychoeducational parent groups). Randomisation is conducted on blocks of 10–18 families on a ratio of 1:1, resulting in groups of 5–9 families in each treatment arm for any block. The randomisation algorithm is run by an independent statistician within the Biostatistics and Health Informatics Department, IoPPN, King’s College London. Details of this are recorded in a separate randomisation specification document. Intervention allocation is emailed only to the group facilitators to ensure that the researchers are blinded to condition.

Measures are collected at baseline, up to 2 months prior to the planned randomisation date and approximately 18–24 weeks after randomisation once the 12-week intervention has finished. Group differences in outcomes will be examined.

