### Sample size justification

As this is a pilot RCT, a formal sample size calculation was not undertaken. We are recruiting 60 families into the pilot RCT. We expect that retention will be approximately 90%, as reported by other trials of psychological intervention conducted with parents of young autistic children. We expect a more modest ES than the 1.3 reported by Sofronoff *et al*
19 as this was for a parent-reported measure and therefore unblinded. For the comparison of Predictive Parenting and the attention control condition, power was calculated by a non-central χ^2^ method using a linear mixed model with baseline (baseline-outcome correlation assumed 0.7) as covariate for two-tailed p=0.05, and intraclass correlation for within intervention group of 0.02 and 10% drop-out. For an ES of 0.5, our study has an expected 95% CI of 0.08, 0.92 and power of 64%, while for an ES of 0.6 the expected 95% CI is 0.18, 1.02 and 79% power.

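### Dummy variables cannot account for clustering by therapy group, because every group lies inside one arm: the arm effect is either not identified or its standard error leaves out the clustering

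*Protocol article*

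**What the plan says.** The protocol article's Statistical analyses section sets the primary comparison as a regression "using analysis of covariance (ANCOVA) regression predicting outcome where post intervention is also covaried for baseline". It then says "Dummy variables will be used to account for randomisation stratification and the clustering effects of groups", and secondary outcomes are to be analysed in the same way. A mixed or structural equation model appears only as the alternative when floor effects are found, and its stated purpose is to handle censoring.

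The layout of the groups comes from two other sections:
- Trial design: "Randomisation is conducted on blocks of 10–18 families on a ratio of 1:1". The section describes the outcome of that split as "resulting in groups of 5–9 families in each treatment arm for any block".
- Procedure: "the groups are run separately with parents of minimally verbal and verbal children within each of our localities".

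The Sample size justification uses a different model. Power there comes from a linear mixed model with baseline as covariate (baseline–outcome correlation 0.7) and an "intraclass correlation for within intervention group of 0.02 and 10% drop-out". For effect sizes of 0.5 and 0.6 it states power of 64% and 79%, with expected 95% intervals of 0.08 to 0.92 and 0.18 to 1.02.

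**The concern.** Randomisation strata and blocks are crossed with arm: each contains families from both arms, so dummies for them are a sound adjustment. Therapy groups are different. Each receives one intervention only and lies wholly within one arm. A fixed effect for every therapy group therefore uses up all the between-arm information. A fixed effect for block does nothing about two families being alike because they sat in the same group.

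What is at stake is the standard error and interval for the primary outcome and for every secondary outcome. The second aim of the trial is an effect size to power a larger trial. That trial would also be delivered in groups, and a dummy-variable model gives it no direct estimate of the group ICC.

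**Working it through.** **Inputs from the article**
- 60 families, 1:1, 10% drop-out: 30 × 0.9 = 27 analysed per arm, 54 in all.
- Baseline correlation 0.7, so the outcome variance left after baseline adjustment is 1 − 0.7² = 0.51 (total variance 1).
- ICC 0.02, two-sided 5%.
- Groups of 5–9, with a planned size of eight after the feasibility phase, so about m = 7 analysed per group.

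**Assumption.** The number of groups is not given. Blocks of 10–18 imply 60/18 = 3.3, so at least 4 blocks, and at most 60/10 = 6. That is 8 to 12 groups. The main calculation uses 8 groups of 6–7 analysed families; 12 groups is shown as the other end.

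**Step 1: reproduce the plan's figures.** With the ICC on the total-variance scale:
- v = 0.51 + (7 − 1) × 0.02 = 0.63
- SE = √(2 × 0.63 / 27) = 0.216
- 95% half-width = 1.96 × 0.216 = 0.42
- Intervals 0.08 to 0.92 and 0.18 to 1.02; power 64% and 79%

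This agrees with the article. Without clustering, SE = √(2 × 0.51 / 27) = 0.194 and power would be 73% and 87%. So the published figures include the clustering, and 0.194 / 0.216 = 0.90.

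**Step 2: therapy-group dummies beside arm.** The dummies for the groups in one arm add up to that arm's indicator.

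| Groups | Columns (intercept, arm, all but one group dummy) | Rank |
|---|---|---|
| 8 | 9 | 8 |
| 10 | 11 | 10 |
| 12 | 13 | 12 |

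The arm coefficient is not identified in any layout. If the software drops a column, what is left is a contrast of one reference group with another. Its SE is about √(2 × 0.51 / 7) = 0.38, against 0.19 for the whole arms, and its value depends on which groups happen to be the reference.

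**Step 3: versions in which the arm effect is estimable.** One option is to average the group coefficients within arm. The other is to use block dummies (intercept, arm, baseline and 3 block dummies: 6 columns, rank 6). Either way, the arm contrast contains between-group variation that the model's SE does not count. Simulated two-sided type I error at a nominal 5%, with 54 families in 8 groups and 10,000 null trials per row:

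| Between-group variance (total = 1) | Block dummies | Averaged group dummies | Paired comparison of group means, 3 df |
|---|---|---|---|
| 0 | 4.9% | 4.9% | 5.0% |
| 0.02 (plan's value) | 7.8% | 7.8% | 4.9% |
| 0.05 | 12.3% | 13.0% | 5.0% |
| 0.10 | 20.1% | 21.9% | 4.9% |

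With 12 groups the dummy-variable analyses give about 7%, 10% and 16% at 0.02, 0.05 and 0.10.

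**Analytic check at 0.02.** With 54/8 = 6.75 per group, true SE / model SE = √((0.51 × 0.98 + 6.75 × 0.02) / (0.51 × 0.98)) = 1.127. The normal-theory type I error is 8.2%, in line with the simulation.

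**The case against.** Five points can be made for the plan.

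- **The dummies may be block dummies.** The article does not define them. On that reading the arm effect is identified and its point estimate is unbiased, and a dropped column would be visible to any statistician. This is fair: the arbitrary contrast is the less likely outcome. It does not rescue the sentence, because block dummies do not account for clustering by therapy group.
- **The size is modest on the plan's own ICC.** This stands. Values of 0.05 and 0.10 are not in the article and serve only as a sensitivity range. If the 0.02 applied to the residual variance instead, the SE ratio √(1 + (m − 1) × 0.02) would be 1.03 to 1.06 for m = 4.5 to 6.75, with type I error of about 5.8% to 6.3%. That scale gives power of 68% and 83% at m = 7, so it does not reproduce the stated 64% and 79%.
- **This is a pilot.** The article disclaims efficacy conclusions, so type I error drives no decision. That lowers the stakes, but an effect size with an honest interval is a stated aim. Estimating the ICC is not a listed aim, and so few groups would estimate it imprecisely.
- **The remedy costs precision.** This stands, and the cost is given with the fix.
- **A separate statistical analysis plan exists and may be sound.** It is not shown. If it specifies a suitable model, the article still misdescribes the primary analysis. Naming the method for clustering is a stated choice, not a detail left to another document.

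**Conclusion.** The concern holds: the sentence is wrong as written. On no reading do dummy variables account for clustering by therapy group in this design. Either the arm effect is not identified, or its standard error omits between-group variance. The sentence also departs from the mixed model on which the article's own power and intervals rest.

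At the plan's ICC of 0.02 the standard error is about 10% too small and type I error is about 7–8%. If groups differ more than planned, the error grows to 10–13% at 0.05 and 16–22% at 0.10. These figures assume 54 analysed families, 8 to 12 groups and a baseline correlation of 0.7. The rank deficiency depends on none of these. The fault is limited to the clustering part of the sentence; dummies for stratification are right.

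**What to change.** Replace the sentence with text such as: *The primary analysis is a linear mixed model fitted by restricted maximum likelihood, with fixed effects for arm, baseline score and the randomisation strata (verbal ability, locality), and a random intercept for therapy group nested in arm. Kenward–Roger or Satterthwaite degrees of freedom will be used. If the model does not converge, baseline-adjusted therapy-group means will be compared between arms. The group ICC will be reported with its confidence interval.* Apply the same group structure to the secondary outcomes and to the floor-effect model. State explicitly whether strata or blocks are the fixed terms, because this sets the degrees of freedom.

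The change is one of wording, and the article describes approval of the analysis plan as still to come. The statistical cost is wider intervals. In the strictest case (4 blocks fitted as fixed effects, 3 degrees of freedom, critical t 3.18), the half-width at SE 0.216 rises from 0.42 to 3.18 × 0.216 = 0.69, and power at effect size 0.5 falls from 64% to about 36%. Two stratum main effects in place of four blocks leave 8 − 4 = 4 degrees of freedom with 8 groups (critical t 2.78, half-width 0.60), and more groups leave more. For a pilot that disclaims efficacy conclusions, that loss is acceptable, and the interval then reflects what this number of groups can show.

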### Economic evaluation

The cost for each participant in the pilot will be derived by the product of the quantity of each service and support used and the unit cost of each of them. Unit costs will be based on the economic notion of opportunity costs—which considers the value of the resource in its next best alternative use. Where this is not practicable, unit costs will be approximated by nationally representative health and personal social services tariffs. Where unit costs are not readily available from such sources, we will derive costs using approaches outlined in an annual compendium of *Unit Cost of Health and Social Care*. We will use the most recent publication of the *Unit Cost of Health and Social Care* produced by the Personal Social Services Research Unit at the time of analysis. All other reported costs will be consistent with the price level used in that edition.^40^

When applying unit costs to unpaid care, we will use other approaches such as replacement costs. Under this approach, unpaid care by family and other carers will be costed using the average hourly rate for a local authority home care worker as the assumed cost for each hour of unpaid informal care.

Consistent with the outcome analyses, the economic evaluation will also conduct an intention-to-treat analysis, including all participants who were randomised. We will compute and compare comprehensively measured costs (for each of the two perspectives adopted: health and social care, public sector or societal) for the two interventions. Under each perspective, the cost-effectiveness analyses will bring together costs and the primary outcome and will compute indicative incremental cost-effectiveness ratios and net benefits; the societal perspective will be adopted in the main analyses. In a secondary economic evaluation, QALY gains computed from parental EQ-5D- scores will be compared with costs from each perspective; again, the societal perspective will be adopted to facilitate comparisons with the main analyses. Other exploratory cost-effectiveness analyses will examine other outcomes and perspectives.

In each case, an incremental cost-effectiveness ratio will be computed as the mean cost difference between Predictive Parenting and the attention control condition divided by the mean difference in change in measures of outcome respectively. If one treatment is indicating it is likely to be both more effective and costlier than the other, we would consider if it is worth incurring the higher costs in order to achieve the improved outcomes. The approach we will employ to reveal the nature of trade-offs such as these—and to represent the inherent uncertainty in any evaluation—will be to plot cost-effectiveness acceptability curves generated from bootstrap analyses. Sensitivity analyses will explore the impact of key assumptions such as the costing of unpaid care time and lost productivity, and the choice of outcome.

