**Health economics measures**				
ONS personal well-being	✓		✓	Parent
EQ-5D quality of life	✓		✓	Parent
CSRI	✓		✓	Parent/blinded researcher
Facilitator time use		✓		Clinician

ABAS–3, *Adaptive Behaviour Assessment System*, third edition; ABC, aberrant behaviour checklist; ACB, assessment of concerning behaviour; ADOS–2, *Autism Diagnostic Observation Schedule*, second edition; APSI, Autism Parenting Stress Index; CAPES-DD, Child Adjustment and Parent Efficacy Scale-Developmental Disability; CGI-I, clinical global impression-improvement; CSRI, Client Service Receipt Inventory; HSQ-ASD, Home Situations Questionnaire-Autism Spectrum Disorders; ONS, Office of National Statistics; OSCA–AB, Observation Schedule for Children with Autism-Anxiety and Behaviour; PASR, Preschool Anxiety Scale Revised; PS, Parenting Scale; SCQ, Social Communication Questionnaire; SWEMWBS, Short Warwick-Edinburgh Mental Well-being Scale.

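### The ICER is written as a mean cost difference over a difference in change scores, which does not match the baseline-adjusted ANCOVA used for the same primary outcome

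*Protocol article*

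**What the plan says.** Economic evaluation gives one formula for all the ICERs: the "mean cost difference between Predictive Parenting and the attention control condition divided by the mean difference in change in measures of outcome respectively". Uncertainty is to be shown by the decision "to plot cost-effectiveness acceptability curves generated from bootstrap analyses". The main cost-effectiveness analysis uses the trial's primary outcome, and a secondary one uses QALYs from the parents' EQ-5D. The section names no baseline or stratification term for costs or effects.

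Statistical analyses describes the effect on that same primary outcome as estimated "using analysis of covariance (ANCOVA) regression predicting outcome where post intervention is also covaried for baseline", with dummy variables for stratification and for group clustering. Secondary outcomes are treated the same way.

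The baseline values needed for adjustment exist. Table 3 schedules the observed primary outcome and the row "EQ-5D quality of life" at baseline and post intervention. Under Health economic measures, the adapted CSRI "measures service use and cost-related impacts at baseline and post intervention".

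**The concern.** A difference in mean change subtracts baseline with a coefficient fixed at 1. ANCOVA estimates that coefficient, which is about 0.7 on a standardised scale if the plan's assumed correlation holds and the SD is the same at both visits. The two agree only if the arms happen to have equal baseline means. Otherwise the effect in the ICER, the net benefit and the acceptability curve will not be the effect the trial reports for its primary outcome.

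The numerator raises a related point. Service costs before treatment usually predict costs afterwards, and they are collected, but the formula gives only a mean cost difference. One of the trial's three aims is to give preliminary cost-effectiveness estimates for planning a larger trial, so avoidable noise in these figures would carry into that planning.

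**Working it through.** **Inputs.** From Sample size justification: 60 families, 10% drop-out, baseline-outcome correlation r = 0.7, intraclass correlation 0.02, two-sided 5% level. From Trial design: 1:1 allocation and 5 to 9 families per therapy group. That gives 30 per arm randomised and 27 analysed. I take a group size of m = 7, the midpoint, as an assumption. All variances are in units of the outcome's total variance, assumed equal at the two visits.

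**1. Reproduce the plan's figures (ANCOVA).**
- Variance = (1 − r²) + (m − 1) × ICC = 0.51 + 6 × 0.02 = 0.63.
- SE = √(2 × 0.63 / 27) = 0.216.
- Effect size 0.5: 95% CI 0.5 ± 1.96 × 0.216 = 0.08 to 0.92; power = Φ(0.5/0.216 − 1.96) = 63.9%. The plan states 0.08 to 0.92 and 64%.
- Effect size 0.6: 0.18 to 1.02 and 79.3%. The plan states 0.18 to 1.02 and 79%.

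The inputs are therefore understood correctly, and the plan's stated precision is that of a baseline-adjusted analysis.

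**2. Change score, same inputs.**
- Without the cluster term: variance = 2(1 − r) = 0.60 against 0.51. Ratio 0.60/0.51 = 1.18; SE ratio √1.176 = 1.085 (0.211 against 0.194).
- With the cluster term: 0.60 + 0.12 = 0.72 against 0.63. SE = √(2 × 0.72 / 27) = 0.231 against 0.216, a ratio of 1.07.
- At effect size 0.5: CI about 0.05 to 0.95 instead of 0.08 to 0.92; power 58% instead of 64%.

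**3. Gap between the two estimates for a given baseline imbalance.**
- SE of the chance imbalance in baseline means = √(2/30) = 0.258 SD.
- Gap = (1 − r) × imbalance = 0.3 × 0.258 = 0.077, about 0.08 SD.
- That is about 15% of an effect of 0.5, or roughly a third of one SE (0.077/0.231 = 0.33).

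Steps 2 and 3 show the same loss in two ways: the excess variance, 0.60 − 0.51 = 0.09, equals (1 − r)² = 0.3². They should not be added together.

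**4. Costs.** The article gives no baseline-to-follow-up correlation for cost. Variance of the unadjusted relative to the adjusted difference = 1/(1 − r_c²):

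| Assumed r_c | Variance ratio | SE ratio |
|---|---|---|
| 0.3 | 1.10 | 1.05 |
| 0.5 | 1.33 | 1.15 |
| 0.7 | 1.96 | 1.40 |

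**The case against.** The strongest reply is that the formula gives the form of the ratio and not the estimator of its parts. A regression-adjusted arm difference is still a mean difference. Statistical analyses itself introduces its ANCOVA with the words "We will test for a between-group change in the primary outcome at post intervention", so a difference in change may be loose wording for the adjusted effect. The article also refers to a separate statistical analysis plan, not available here, and the covariates of cost and QALY models are commonly left to such a plan. The ICERs are called indicative, and the article says efficacy conclusions are not possible.

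Much of this stands, and it rules out several stronger readings that a reader might infer:

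- *That the components are raw or unadjusted.* The article uses neither word.
- *That baseline is discarded.* A change score uses baseline, with a fixed coefficient.
- *That the denominator is biased.* Over repeated randomisations it is not. The 0.08 SD is a gap conditional on one realised imbalance.
- *That the article breaks its own promise of consistency.* The sentence reads "Consistent with the outcome analyses, the economic evaluation will also conduct an intention-to-treat analysis, including all participants who were randomised". It promises a common analysis population and does not mention models or covariates.
- *That a large loss of precision in costs has been shown.* That range rests on assumed correlations.

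The objection does not remove the mismatch. The sentence in Statistical analyses explains its own use of change by naming ANCOVA. The ICER formula has no such qualifier, and a health economist who followed it literally would compute change scores.

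**Conclusion.** The point holds as a mismatch between a stated economic estimator and the stated main analysis, with a modest loss of efficiency if the formula is followed as written. For the effect, the loss is a variance ratio of 1.18 at r = 0.7, or an SE about 7% larger with the cluster term and 8.5% larger without it. The typical gap between the ICER's effect and the reported effect is 0.08 SD. These figures rest on the plan's own correlation and sample size, equal SDs at both visits and, for the 7%, an assumed group size of 7. A lower correlation would increase the loss: at r = 0.5 the variance ratio is 1.00/0.75 = 1.33.

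For costs the loss could be larger or smaller, at 1.10 to 1.96 times the variance for assumed correlations of 0.3 to 0.7. The article states nothing wrong there; baseline cost is simply not mentioned. The primary and secondary outcome analyses are unaffected.

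**What to change.** Amend the ICER definition to say that:

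- the incremental effect is the baseline-adjusted arm difference, with the post-intervention outcome regressed on arm, baseline and the stratification factors as in the main analysis, and signed so that a fall in challenging behaviour counts as benefit;
- the incremental cost is the arm difference adjusted for baseline CSRI cost;
- the QALY difference is adjusted for baseline EQ-5D;
- the adjusted models are refitted in each bootstrap sample, so that the acceptability curves reflect the same estimators.

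The choice of joint model for costs and effects, and whether to resample by therapy group, can be left to the analysts. With groups of 5 to 9 families, 60 families form only about 7 to 12 groups (60/9 to 60/5), which is few for resampling by group. If the clustering dummies of the main analysis are indicators for individual therapy groups, they should not be carried over without checking. Such groups are nested within arm, and their indicators could absorb the arm effect.

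The cost is a few sentences in the plan and minor extra analysis work. No new data are needed.
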